### Study design

This study underwent peer review by the funding body, the National Health and Medical Research Council*.* This study will consist of a prospective cohort study comparing:*Maternal and infant health outcomes*: women booked to receive maternity care through MMH or RBWH, by model of care and Aboriginal and Torres Strait Islander status of baby and/or mother (see Table 3). Routinely collected clinical outcomes for mothers and infants will provide data on the effectiveness of the programs since they commenced in late 2013 and be compared across groups for the duration of the study (ending in 2019), and to baseline data for both hospitals (2009–2013). Infant assessments will be undertaken at two and 6 months postnatally for Groups 1 and 4.*Service acceptability, effectiveness and cost-effectiveness:* Maternal surveys will be undertaken as early as possible antenatally (~ 20 weeks and 36 weeks antenatally, two and six months postnatally). An ethnographic component will also explore the pregnancy and early parenting (to six months postnatal) experiences of ~ 20 women from each Birthing in Our Community and the Ngarrama Service using a longitudinal, ethnographic approach: ‘Tell My Story’ substudy. Cost-effectiveness analysis will be conducted from the broader ‘societal’ perspective which will include not only the cost to the hospital (Routine data) but the cost to the women (Women’s surveys) and partner organisations (Routine data).*Service sustainability and feasibility:* Staff perspectives and experiences will be compared across the services to determine the sustainability and feasibility from a workforce perspective.

**Table 3 Tab3:** Timeline of groups by model of care and research data available

Year	2009	2010	2011	2012	2013	2014	2015	2016	2017	2018	2019
Groups by model of care						Group 1: Birthing in Our Community, MMH (Indigenous)					
	Group 2: Standard care, MMH (Indigenous)										
	Group 3: Standard care, MMH (Non-Indigenous)										
						Group 4: Ngarrama Indigenous Maternity Service, RBWH (Indigenous)					
	Group 5: Standard care, RBWH (Indigenous)										
	Group 6: Standard care, RBWH (Non-Indigenous)										
Research data (Groups)	*Baseline*					*Study period*					
	Routine Data (2, 3, 5, 6)					Routine Data (1–6)					
						Women’s Surveys (1, 2, 4, 5)					
						Tell My Story (1, 4)					
						Infant Assessments (1, 2, 4, 5)					
						Staff Interviews (1, 4)					

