##### Routinely collected clinical and costing data (Groups 1–6)

Women and infants will be excluded if they have been transferred into the RBWH or the MMH from out of area for high-level specialist services or received no antenatal care.

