#### Secondary outcome measures (all groups where reliable data is available)

Gestation at first antenatal visit to a health provider, at booking into hospital (weeks, Mean, Median, Range, First trimester (Yes/No)), Number of total antenatal visits (Mean, SD, Median, Range, < 5 visits, 5 and more visits)The proportion of women with modifiable risk factors for preterm birth (i.e. inadequate antenatal care, smoking, stress and missing data in these fields)Smoking status at booking (Yes/No), during the first 20 weeks (Yes/No), and after the first 20 weeks (Yes/No), at discharge and six months postnatal, Number of cigarettes intake each day if smoking (Mean, SD)The proportion of women who attended antenatal education sessions (Yes/No)Pharmacological analgesia in labour (Epidural/spinal analgesia, Narcotic analgesia, Nitrous oxide gas)Onset of labour (Induced, No labour, Spontaneous)Mode of birth (Non-instrumental vaginal birth, Instrumental vaginal birth, Elective Caesarean section, Emergency Caesarean section)Management of third stage labour (Active, Physiological)Postpartum haemorrhage (< 500; 500–999; 1000-1499; 1500 ml and more or with blood transfusion)Perineal trauma status (Intact/1st degree tear, 2nd degree tear, 3rd/4th degree tear).Episiotomy (Yes/No)Women who had a known caregiver for labour and birth (Yes/No)Birth weight (grams, Mean, SD, < 2500 g, 2500 g or more)Apgar score 5 min (< 7, 7 or above)Admission to a separate neonatal nursery (Yes/No)Perinatal outcomes (Liveborn survived, Liveborn neonatal death prior to discharge from hospital, Stillbirth)Cause of perinatal deathsAntenatal intention to breastfeed (Yes/No)Women exclusively breastfeeding at discharge from hospital following birth (Yes/No), at two months postnatal (Yes/No), and six months postnatal (Yes/No)Mother readmission to hospital up to six months postpartum (Yes/No)Infant readmission to hospital up to six months of age (Yes/No)Length of stay in hospital for mothers and infants following birth (Mean, Median, Range)Cost of care per mother/infant pair during pregnancy, birth, postnatal until mother six weeks postpartum and baby 28 days after birthNegative life events scale – full extended version – at booking-in and six months postnatal (Yes/No, Number of events)Modified Kessler Psychological Distress Scale (K5) score at booking-in, 36 weeks gestation, two and six months postnatalEdinburgh Postnatal Depression Scale score at booking-in and six months postnatalAges and Stages Questionnaire score at two and six months postnatalBayley III Cognitive, Language and Motor Skills score at six months postnatal

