### Data analysis and management

#### Quantitative

Clinical data will initially be collected in a re­identifiable form (via the unique patient identifier) so that it can be linked with data obtained from other sources (e.g. surveys), to enable the economic analyses to be undertaken. Once merged, identifiers will be removed and only the coded number will remain.

Quantitative analyses will compare the difference in clinical outcomes between Birthing in Our Community (intervention), the Ngarrama Service (concurrent control), standard care (historical and concurrent control), and also non-Indigenous women and babies (historical and concurrent control) at MMH and RBWH.

Data on all women attending either hospital during the study period will be extracted. Women transferring in from other hospital or rural and remote areas for higher-level services (variable available), and those with no antenatal care will be excluded from analysis. Analyses will be by birth model of care and women with multiple births and their infants with identified fetal anomaly will be excluded from analysis unless noted otherwise.

Initial bivariate analysis will investigate possible differences between the cohorts for baseline socio-demographic (socio-economic status), and clinical characteristics (e.g. age, parity, body mass index, smoking, obstetric history) that could affect outcome measures. Dependent on data type, analysis will be undertaken using an independent samples t-test, Mann-Whitney U test or chi-squared test. Outcome measures will be presented using relative risks with 95% confidence intervals. Multivariate logistic, linear regression models and propensity score matching will be used to adjust for confounders. Longitudinal outcomes (e.g. breastfeeding) will be analysed with generalized estimating equations to account for the correlation between observations repeated in the same person. To understand the mechanism or process that underlies the effect of model of care on outcomes, mediation analysis will be conducted to identify if and to what extent the other variables explains the relationship. All withdrawals, losses to follow-up, and deaths will be reported. Analysis will be performed with SPSS Version 22.0/Stata 14.0 and statistical significance will be at the 0.05 level.

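### Excluding women with no antenatal care from the routine data selects on a primary outcome, five or more antenatal visits, and may understate a gain in access against baseline

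*Protocol article*

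**What the plan says.** The Protocol article, under Primary outcome measures, lists the proportion of women with five or more antenatal visits as one of four primary outcomes for all groups.

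Under Data analysis and management, Quantitative, the source population is broad: "Data on all women attending either hospital during the study period will be extracted". The same paragraph then removes transfers in, and adds that "those with no antenatal care will be excluded from analysis". The eligibility section on routinely collected clinical and costing data (Groups 1–6) states the same rule: "Women and infants will be excluded if they have been transferred into the RBWH or the MMH from out of area" for specialist services, "or received no antenatal care".

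The only qualifier nearby belongs to a different exclusion, in the next sentence: "women with multiple births and their infants with identified fetal anomaly will be excluded from analysis unless noted otherwise". It makes no exception for the visit outcome.

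The secondary outcomes include the total number of visits, with a split at five, and the modifiable risk factors "inadequate antenatal care, smoking, stress and missing data in these fields". These use the same restricted data. Aims and Study design commit the study to comparison with 2009–2013 baseline data from both hospitals as well as across models of care.

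**The concern.** No visits is the extreme of fewer than five. Removing these women deletes certain failures from the denominator of a primary outcome, cuts the visit count off at zero, and takes the clearest cases out of the inadequate-care measure.

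The exclusion also sits close to what the services try to change. The Background presents the antenatal period as the target and cites evidence that preterm birth and perinatal death fall as consultations rise. If a new service reaches women who would formerly have had no care, they are counted in the study period while their counterparts at baseline are deleted. The step from no care to some care then cannot appear in the results.

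**Working it through.** **The plan's own figure.** Table 4 plans a change from 81.0% to 90.0% with power 0.924. With 350 per arm, two-sided 0.05 and pooled variance without continuity correction:
- standard error under no difference: √(2 × 0.855 × 0.145 / 350) = 0.0266
- standard error under the alternative: √((0.81 × 0.19 + 0.90 × 0.10) / 350) = 0.0264
- z = (0.09 − 1.96 × 0.0266) / 0.0264 = 1.43, so power = 0.924, as stated.

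The 261 per cohort in that row is the continuity-corrected number for 80% power. This does not bear on the point here.

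**Effect on a single rate.** If a share u of a group had no visits and p is the rate in all women, the plan reports p/(1 − u). With u = 2%, 81% becomes 82.7%. With u = 5%, it becomes 85.3%.

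**Effect on a difference.** Let a0 and a1 be the rates among women with some care at baseline and in the study period, and q0 and q1 the shares with no care.
- The plan estimates a1 − a0.
- The difference in all women is a1(1 − q1) − a0(1 − q0).
- The shortfall is a0·q0 − a1·q1.

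The direction therefore depends on how far the no-care share falls. With 81% and 90%, the absolute difference is understated once that share falls by more than about a tenth (0.81/0.90 = 0.90). If the share does not fall, the relative risk stays at 1.111. The absolute difference is then slightly overstated: 9.0 points reported against 8.8 (2%) or 8.6 (5%) in all women.

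**Illustration.** Three inputs are assumptions and not in the article: q of 2–5% at baseline, halved in the study period, and half of the newly engaged women reaching five visits. The 81% and 90% from Table 4 are applied to the remaining women.

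| | q = 2% | q = 5% |
|---|---|---|
| Baseline, all women: 0.81(1 − q) | 79.4% | 77.0% |
| Study period, all women: 0.90(1 − q) + 0.5·q/2 | 88.7% | 86.8% |
| True difference | 9.3 points | 9.8 points |
| Study period as analysed: divide by (1 − q/2) | 89.6% | 89.0% |
| Difference as analysed (baseline 81%) | 8.6 points | 8.0 points |

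**Preterm birth, secondary.** Assume no true effect, 14% preterm among attenders (the national figure in the Background) and 40% among women without care (an assumption), with newly engaged women keeping that risk. The study period would show (0.14(1 − q) + 0.40·q/2)/(1 − q/2) = 14.3% for q = 2% and 14.7% for q = 5%. The crude relative risk is 1.02–1.05. Table 4 plans a change from 16% to 9%, a relative risk of 0.56.

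**The case against.** The strongest defence is that the protocol compares models of care, and a woman with no antenatal care received none. Study design speaks of women booked for care, by model, and Quantitative says that analyses follow the model. Groups 1 and 4 can hold essentially no such women, so applying one rule to all six groups makes them comparable among attenders. This stands for contrasts by model. It does not reach a comparison of whole hospitals over time, where no woman has to be assigned to a model.

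The illustration describes such a hospital-level contrast, which the protocol does not set out explicitly. That stands too: the 8.6–8.0 points are not the bias in Group 1 or Group 4 against standard care.

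A reader might infer that the cure is to count these women as standard care, and that leaving them out costs the study much of its power. The documents do not support this. Placing them in standard care loads certain failures on one side. With no true effect, 81% in both groups among attenders and q of 2–5%, standard care would show 79.4–77.0%, a spurious relative risk of 1/(1 − q) = 1.02–1.05 in favour of the programmes.

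A reader might also infer that the baseline comparisons of preterm birth and smoking are biased against the service. For preterm birth this rests on risks that the article does not give. The effect is small even so, and it is crude, before the planned regression and propensity adjustment. For smoking, nothing in the document fixes a direction or a size.

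Finally, the absence of a sensitivity analysis is no fault, since an article may leave it to the analysis plan. The point rests on an affirmative rule that the article states.

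**Conclusion.** The point holds for the antenatal-visit outcomes. The exclusion selects on a primary outcome and truncates the related secondary ones. Rates of five or more visits are overstated wherever women without care existed, and a gain in access against 2009–2013 may be understated.

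The size cannot be determined from the document. Under the assumptions shown, about 0.7 to 1.8 points of a 9.3–9.8 point hospital-level difference would be lost. That is modest, and it depends on the no-care share actually falling.

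A small bias in the baseline comparison of preterm birth is possible but secondary. The contrasts by model of care remain valid for a narrower population, women who received some antenatal care.

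**What to change.** - For the antenatal-visit outcomes, lift the exclusion in a hospital-level comparison of baseline with study period among women having Aboriginal and Torres Strait Islander babies. Count women with no antenatal care as having fewer than five visits.
- Confirm that the 2009–2013 extract includes these women. The article promises a full extract only for the study period.
- Keep the exclusion as the main analysis for contrasts by model of care and for the surveys. State that these results apply to women who received some antenatal care.
- Report the number excluded for this reason by group and period.
- If women with no visits are ever placed in standard care, label that as a bounding analysis only, because it favours the programmes by construction.

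The cost is a change of wording, a check of the baseline extract and one extra analysis. The downside is that a hospital-level contrast dilutes the programme effect, because not all eligible women use the new services.

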In developing the evaluation of the Birthing in Our Community program we aimed to compare outcomes for mothers and infants with a similar cohort of women receiving standard care. After reviewing the statistics from across South East Queensland, the most appropriate comparison cohort was women attending the Royal Brisbane and Women’s Hospital (RBWH) where senior managers and researchers agreed to collaborate on a joint project and funding submission. However, as the funding was being awarded, the RBWH also changed their model of care (2013) for Aboriginal and Torres Strait Islander women through the Ngarrama Indigenous Maternity Service and it is no longer standard care. The Ngarrama Service is a government-funded midwifery continuity of care service for women having an Aboriginal and/or Torres Strait Islander baby/ies and planning to birth at the RBWH (located fewer than six kilometres north of the MMH). Thus we have agreed to evaluate both new services, Birthing in Our Community and the Ngarrama Service, and will compare them to each other, and to women receiving standard care and to baseline data from both hospitals. (Note: not all women having Aboriginal and Torres Strait Islander babies at both MMH and RBWH access the Indigenous-specific models of care hence the concurrent comparison with standard care). Table 2 outlines the components of the different models of care available to women having Aboriginal and Torres Strait Islander babies at the MMH and RBWH. For the first time, researchers will test the effectiveness of caseload midwifery in an urban setting where 100% of the midwives’ caseload are women having Aboriginal and Torres Strait Islander babies receiving care across the maternity continuum (antenatal, birth, until 6 weeks postnatal).

**Table 2 Tab2:** Models of care available to Aboriginal and Torres Strait Islander families at study sites

Birthing in Our Community (Group 1)	Standard Care (Groups 2, 5)	Ngarrama Maternity Service (Group 4)

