### Study participants

#### Inclusion/exclusion criteria

##### Women’s surveys, Tell My Story and Infant Assessments

Women are eligible to participate if they:Are having an Aboriginal and/or Torres Strait Islander baby;Receive their maternity care through the Birthing in Our Community program and are planning to birth at the MMH (Group 1); receive their maternity care through the Ngarrama Indigenous Maternity Service and are planning to birth at the RBWH (Group 4); receive standard maternity care and birth at the MMH or RBWH (Groups 2 & 5); andConsent to participate.

Women are not eligible to participate if they:Have been transferred into the RBWH or the MMH from out of area for high-level specialist services or received no antenatal care.

Infants are eligible if:They are Aboriginal and/or Torres Strait Islander and their mothers received care through either of these hospitals and were recruited to the study.

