#### Power and sample size

This study has been powered to detect changes in clinical outcomes and the number of women accessing care per annum in each program [33]. During the 3.5-year recruitment period, we will aim to access routinely collected data for approximately 420 women at MMH, and 350 from RBWH (based on an estimated 20% attrition rate). The change in outcomes has been estimated based on changes seen in the Townsville Mums and Bubs program that reported a reduction in preterm birth [34] (Table 4).

**Table 4 Tab4:** Power calculations with *n* = 350 in each arm + 20% for attrition

Outcome	From %	To %	No./ cohort	Power
Proportion of women who attend ≥ 5 antenatal visits	81.0	90.0	261	0.924
Proportion of women who were smoking after 20 weeks	42.0	31.0	318	0.858
Preterm birth < 37 weeks pregnancy	16.0	9.0	350	0.801
Exclusive Breast feeding at discharge (2007–09 Mater data)	78.0	88.0	240	0.942

The sample size for the ethnographic component of the study (‘Tell My Story’) will involve a smaller group of women from each cohort. The project aims to recruit up to 25 women from each cohort, which factors in a 20% attrition rate (25*.8 = 20).

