### Outcome measures

#### Primary outcome measures (all groups)

Proportion of women giving birth preterm (< 37 weeks gestation)Proportion of women who attend five or more antenatal visits during pregnancyProportion of women smoking after 20 weeks gestationProportion of women exclusively breast-feeding at discharge from hospital.

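### Grouping women by model of care at birth settles exposure when preterm birth occurs, so a preterm benefit can appear without any true effect

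*Protocol article*

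**What the plan says.** The grouping rule for the clinical outcomes is in the protocol article, Data analysis and management, Quantitative: "Analyses will be by birth model of care and women with multiple births". The rest of that sentence deals with exclusions.

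Study design describes the cohort as "women booked to receive maternity care through MMH or RBWH, by model of care". Study setting explains where the concurrent standard-care group comes from: "not all women having Aboriginal and Torres Strait Islander babies at both MMH and RBWH access the Indigenous-specific models of care". Access to a programme is therefore neither universal nor randomised.

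Preterm birth is one of four unranked primary outcomes. In Table 4 the row "Preterm birth < 37 weeks pregnancy" plans for a fall from 16.0% to 9.0% with 350 women per cohort and power 0.801.

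The article does not say how to classify a woman who changes model during pregnancy, or who gives birth before she could enrol. It sets no gestational landmark and no analysis by model at booking or enrolment. The routine-data exclusions cover women transferred in from out of area and women with no antenatal care, not movement between models. Confounding is to be handled by regression and propensity score matching. The baseline characteristics named are socio-economic status, age, parity, body mass index, smoking and obstetric history.

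**The concern.** Exposure should be fixed before the outcome can influence it. Model at birth is known only once the pregnancy has ended, and how early it ended is the outcome. Misplacement can arise in two ways:

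- A woman enrolled in a programme who leaves it before birth is counted under another model.
- A woman who would have enrolled at, say, 24 weeks but gives birth before then can never be a programme birth. Enrolled women have by definition stayed pregnant until enrolment (immortal time).

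If either happens more often in pregnancies that end early, preterm births drain from the programme group. In the concurrent comparison they are also added to standard care, so the gap widens from both sides. In the historical comparison the 2009–2013 groups predate the programmes and keep all their early births, so only the programme side is distorted.

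Matching or adjusting on characteristics measured at baseline does not repair this, because the misplacement is driven by what happens later in pregnancy. At stake is the comparison for which the Discussion specifically claims statistical power.

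**Working it through.** **Inputs from Table 4.** Preterm 16.0% and 9.0%, n = 350 per cohort, stated power 0.801. The 0.05 significance level is in the Quantitative section; two-sided is assumed.

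**The plan's own figure.** With pooled proportion 0.125:

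z = [0.07 − 1.96 × √(2 × 0.125 × 0.875 / 350)] / √[(0.16 × 0.84 + 0.09 × 0.91) / 350] = (0.0700 − 0.0490) / 0.02486 = 0.845

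This gives power 0.801, so the stated figure reproduces.

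**Illustration under no true effect.** Suppose 350 women belong to each model and 16% deliver preterm in both: 56 preterm and 294 other births per model. Let *a* be the share of programme preterm births, and *b* the share of programme other births, that are recorded under standard care at birth. Both are assumptions; the article gives neither.

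- Programme rate = 56(1 − a) / [56(1 − a) + 294(1 − b)]
- Concurrent standard rate = 56(1 + a) / [56(1 + a) + 294(1 + b)]
- Historical standard rate is assumed to be 16% and is unaffected by movement

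| a / b | Programme | Concurrent standard | RR, concurrent | RR, historical |
|---|---|---|---|---|
| 5% / 5% | 53.2/332.5 = 16.0% | 58.8/367.5 = 16.0% | 1.00 | 1.00 |
| 5% / 0% | 53.2/347.2 = 15.3% | 58.8/352.8 = 16.7% | 0.92 | 0.96 |
| 10% / 2% | 50.4/338.5 = 14.9% | 61.6/361.5 = 17.0% | 0.87 | 0.93 |
| 20% / 3% | 44.8/330.0 = 13.6% | 67.2/370.0 = 18.2% | 0.75 | 0.85 |
| 30% / 5% | 39.2/318.5 = 12.3% | 72.8/381.5 = 19.1% | 0.64 | 0.77 |

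The last row gives a concurrent gap of 6.8 points, against the planned 7. It is an extreme case.

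**Chance of a false significant benefit, concurrent comparison.** The same normal approximation, with the observed rates and group sizes put in, gives:

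- 5% / 5%: 2.5%, the nominal level in that direction
- 5% / 0%: 7%
- 20% / 3%: z = [0.0458 − 1.96 × √(0.16 × 0.84 × (1/330.0 + 1/370.0))] / √(0.1358 × 0.8642/330.0 + 0.1816 × 0.8184/370.0) = (0.0458 − 0.0544)/0.0275 = −0.31, that is 38%

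In the 20% / 3% row, 0.20 × 56 + 0.03 × 294 = 11.2 + 8.8, or about 20 women, change group. The direction depends only on whether *a* exceeds *b*; if *b* exceeded *a*, the bias would run against the programme.

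**The case against.** The strongest reply is that the article documents no flow of complicated or early pregnancies out of the programme. Table 2 describes programme care running through pregnancy, birth and six weeks postnatally, and lists access to medical and other professionals as required. If specialist input is added while the woman stays enrolled, model at birth equals model at enrolment and that route closes. This stands: a reader might infer that complicated pregnancies are moved to standard care, but nothing says so. It does not close the late-enrolment route, on which the article is silent.

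Three further replies have force:

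- A reader might see a contradiction between "women booked to receive maternity care through MMH or RBWH, by model of care" and the grouping rule. The booking in that phrase is to a hospital. It can define the cohort while the Quantitative section defines the groups, so this is a gap in timing, not two conflicting rules.
- A reader might see an asymmetry in eligibility, since Group 1 requires a planned birth at the hospital while Groups 2 and 5 are worded "receive standard maternity care and birth at the MMH or RBWH (Groups 2 & 5". Those criteria govern the surveys, Tell My Story and infant assessments. The routine data have their own exclusions, the same for all six groups, so the wording does not bear on the preterm analysis.
- The comparison of Group 1 with Group 4 sets two enrolled programmes under one rule, and similar misplacement would tend to cancel.

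The phrase at issue could also be loose wording for maternity model of care. If so, the sentence still needs correcting, since it would then not say when the model is assigned.

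**Conclusion.** The concern holds as a possibility built into the stated rule, not as a demonstrated bias. As written, exposure is settled when the outcome occurs, and no other part of the article limits the consequence. The programme versus standard-care comparison of preterm birth can therefore show a benefit that is not there, and the planned adjustment would not remove it.

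The size cannot be known from the article. Under no true effect the concurrent relative risk runs from 1.00 with non-differential movement, through 0.92 with 5% of programme preterm births alone misplaced, to 0.75 with 20% of preterm and 3% of other births misplaced. These rest on assumed rates, 350 women per model and 16% preterm in both. It would go too far to say that preterm birth does determine the grouping, or that the result will be biased. The text supports only that it can.

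**What to change.** In the Quantitative section, replace grouping by model at birth for the primary preterm analysis with one of the following, using the same rule for Groups 1, 2, 4 and 5:

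- the model in which the woman was booked or enrolled by a fixed gestational landmark (for example 20 weeks), among women still pregnant at that point; or
- delayed entry, with model of care as a time-dependent exposure.

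Grouping by the model first booked, without a landmark or delayed entry, is not enough: a woman who delivers before enrolling would still count as standard care.

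Keep model at birth as a sensitivity analysis, and report switches and late enrolments by group. The survey eligibility wording need not change for this purpose.

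**Cost.** Mainly protocol wording and analysis work. Women who change model or enrol after the landmark dilute the contrast, and births before the landmark drop out of that analysis. The listed secondary outcomes include gestation at booking into hospital, where reliable data exist, but the article does not show that model and date of programme enrolment are recorded. The sponsor must confirm that both can be retrieved from programme or hospital records.

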## Discussion

This study will test the impact of two maternity models of care for one of Australia’s highest priority health populations: Aboriginal and Torres Strait Islander mothers and babies. The model and economic impact assessment have been derived from international best-practice and service evaluations in Australia and our study has the statistical power to detect a difference in preterm birth. The multi-agency approach to implementing a Birthing on Country Service Model at one site has been recommended in Aboriginal and Torres Strait Islander policy documents and will be evaluated. The economic impact assessment aims to quantify the impact of the model by articulating the process by which research leads to impacts on the end-user and/or the broader community. If the model is successful and demonstrates a good return on investment, we will have developed and evaluated a culturally safe service model transferable to other settings for trialling in a broader context.

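### Four unranked primary outcomes are compared across several group contrasts at a flat 0.05, with no lead outcome or lead contrast, so the chance of at least one false significant primary result is well above 5%.

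*Protocol article*

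**What the plan says.** - **Outcomes.** Under the heading "Primary outcome measures (all groups)", the article lists preterm birth, attendance at five or more antenatal visits, smoking after 20 weeks, and exclusive breastfeeding at hospital discharge. None is ranked above another.
- **Contrasts.** The Study setting section says of the two new services that the team "will compare them to each other, and to women receiving standard care and to baseline data from both hospitals". The Quantitative analysis section lists "Birthing in Our Community (intervention), the Ngarrama Service (concurrent control), standard care (historical and concurrent control"), and adds non-Indigenous women and babies as historical and concurrent controls at both hospitals. No comparison is singled out.
- **Error rule.** The only statement is that "statistical significance will be at the 0.05 level". Results are to be shown as relative risks with 95% confidence intervals.
- **Power.** Table 4 gives each primary outcome its own power at 350 per arm. It does not say which two groups are the arms.
- **Emphasis.** The Discussion makes one power claim: "our study has the statistical power to detect a difference in preterm birth". The Study setting section also singles out preterm birth as a target of the partnership. Neither statement makes it the formal lead outcome.

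**The concern.** Aim 4 asks whether women in the new model have better maternal and infant outcomes than women in other models and at baseline. Four outcomes crossed with several contrasts give many chances of a significant result, each at the full 0.05. Nothing says in advance which result answers the aim.

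The contrasts can also disagree. If both new services work, Birthing in Our Community against Ngarrama may show nothing while Birthing in Our Community against standard care or baseline is positive. The Discussion ties transfer of the model to other settings to its being successful. A reader of the final report could not tell whether a highlighted result was the planned test or the most favourable of many.

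**Working it through.** **1. Reproduce Table 4.** Inputs are the From and To percentages in Table 4 and n = 350 per arm. The test is a two-sided comparison of two proportions with pooled variance under the null and no continuity correction:

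power = Φ[(|p1 − p2| − z·SE0) / SE1], where SE0 = √(2·p̄(1 − p̄)/n) and SE1 = √([p1(1 − p1) + p2(1 − p2)]/n).

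For preterm birth, p1 = 0.16, p2 = 0.09 and p̄ = 0.125. SE0 = √(2 × 0.125 × 0.875/350) = 0.0250 and SE1 = √((0.1344 + 0.0819)/350) = 0.02486. At 0.05, (0.07 − 1.96 × 0.0250)/0.02486 = 0.845, so power = 0.801.

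| Outcome | Table 4 | Recomputed, 0.05 | Recomputed, 0.0125 |
|---|---|---|---|
| Five or more visits | 0.924 | 0.924 | 0.814 |
| Smoking after 20 weeks | 0.858 | 0.858 | 0.701 |
| Preterm birth | 0.801 | 0.801 | 0.619 |
| Breastfeeding at discharge | 0.942 | 0.9425 | 0.849 |

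The stated powers match 0.05 for each outcome taken alone. They do not match 0.05/4 = 0.0125, so no allowance for four outcomes is built in. The last column only shows this; it is not a proposal to split alpha.

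**2. One contrast, four outcomes, no true effect.** If the outcomes are independent, the chance of at least one p < 0.05 is 1 − 0.95^4 = 18.5%. In the favourable direction only (0.025 per test) it is 1 − 0.975^4 = 9.6%.

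**3. Several contrasts.** From the Study setting section, five contrasts can be read: Group 1 v 4, Group 1 v 2, Group 4 v 5, and Groups 1 and 4 each against their own hospital's baseline. That makes 4 × 5 = 20 tests, which share groups and women. I simulated normal test statistics (up to 1,000,000 draws) under no effect. With equal group sizes, contrasts that share one group are correlated at ±0.5. The correlation between outcomes is not in the article, so it was varied from 0 to 0.8. The three-contrast row uses Groups 1 v 4, 1 v 2 and 4 v 5.

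| Contrasts (tests) | Direction | Corr. 0 | Corr. 0.5 | Corr. 0.8 |
|---|---|---|---|---|
| 1 (4) | either | 18.5% | 15.6% | 11.4% |
| 3 (12) | either | 42.7% | 36.6% | 27.7% |
| 5 (20) | either | 58.2% | 50.9% | 39.7% |
| 1 (4) | favourable | 9.6% | 7.8% | 5.7% |
| 3 (12) | favourable | 25.2% | 20.6% | 15.4% |
| 5 (20) | favourable | 36.2% | 29.7% | 22.5% |

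A single test has 5% in either direction and 2.5% in the favourable direction. The contrasts with non-Indigenous groups are left out and would add to these figures.

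**4. Naming an outcome is not enough.** Preterm birth alone still gives about 13% over three contrasts and 19.5% over five, in either direction. A lead contrast is needed as well.

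**The case against.** **An unseen plan may settle it.** This is a condensed article, and a full protocol or analysis plan could hold a multiplicity rule. That is fair, and the mere absence of a rule would not be a finding. But the article fixes a flat 0.05, and Table 4 shows that the study was sized on it. A later alpha split would leave Table 4 and the Discussion's power claim out of step: at 0.0125, preterm birth has power 0.619.

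**No success rule and no family-wise promise.** A reader might infer that the study has up to an even chance of falsely declaring success. The article does not support that. It never says that one significant result on any outcome in any contrast counts as success. The Discussion also asks for a good return on investment. The either-direction figures include harmful results, which nobody would call success. This objection stands, so the figures here are chances of at least one false significant primary result, with the favourable direction shown separately.

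**The choice of family is arguable.** The two services are each evaluated, so Group 4 v 5 may be a separate question from Group 1 v 2. In a non-randomised cohort reporting relative risks with intervals, how strictly to control family-wise error is partly a matter of judgement. This also stands, and it is why the one-contrast figures are given. They still exceed the single-test rate.

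**Preterm birth already leads in practice.** It has the largest required number in Table 4 and the only power claim. That supports making it formal; it does not replace doing so.

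**Two side points are tidying only.** Three primaries reappear in the secondary list, for example "Women exclusively breastfeeding at discharge from hospital following birth (Yes/No"), but inside fuller reporting series that add no new primary hypothesis. Ngarrama is both a new service under evaluation and a concurrent control, which is compatible with being an active comparator.

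**Conclusion.** The point holds as a defect in what the article fixes: four unranked primary outcomes, several contrasts, one flat 0.05, and no lead outcome or contrast. The chance of at least one false significant primary result exceeds the single-test rate under every assumption tried. It is about 11.4% to 18.5% for one contrast and 39.7% to 58.2% for five in either direction. For falsely favourable results it is about 5.7% to 9.6% and 22.5% to 36.2%.

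These figures rest on equal group sizes, outcome correlations of 0 to 0.8 and a reading of one to five contrasts. They show scale and are not bounds. The article gives 420 women at one hospital and 350 at the other, but no sizes for the standard-care or baseline groups.

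A reader might also conclude that Group 1 v Group 2 must be the deciding comparison. The article does not support that: no Group 2 size is stated, and aim 4 names both other models of care and baseline. What is needed is that one contrast be named and justified.

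**What to change.** In the primary outcomes section and the Quantitative analysis section:

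1. Name preterm birth as the lead primary outcome. This fits the partnership's target, the largest required number in Table 4 and the Discussion's power claim.
2. Test the other three primaries after it in a stated fixed sequence, each at two-sided 0.05. Confirmatory claims stop at the first non-significant result.
3. Name one lead contrast for the Birthing in Our Community effectiveness claim. The sponsor should choose it before seeing the comparative results, justify it and give its expected group sizes. Same-hospital concurrent standard care (Group 1 v Group 2) is one candidate, but its size must be shown.
4. Report the remaining contrasts as supportive, with estimates and 95% confidence intervals.

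**Cost.** No extra women or data are needed to state the rule. The later primaries support a confirmatory claim only if the earlier steps succeed, and the other contrasts do not support one at all. The sequence takes no alpha from preterm birth, but its 0.801 power depends on the lead contrast. By the formula above, it falls to about 0.74 at 300 per arm and 0.66 at 250. If the chosen contrast is smaller than 350 per arm, the power claim must be restated.
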